# Sutures versus staples for wound closure in orthopaedic surgery: a randomized controlled trial

**DOI:** 10.1186/1471-2474-13-89

**Published:** 2012-06-06

**Keywords:** Wound closure, Orthopaedic surgery, Sutures, Staples, Surgical wound complications, Surgical site infection

## Abstract

**Background:**

A recently published meta-analysis comparing metallic staples to sutures in orthopaedic procedures revealed three fold increase in risk for infection in stapled wounds. The studies included in the meta-analysis are at risk of bias due to experimental design limitations. A large randomized controlled trial is proposed to direct orthopaedic surgeons in their choice of wound closure material.

**Methods/Design:**

A parallel group randomized controlled trial with institutional review board approval will be conducted. Patients will be randomized intraoperatively to have skin wounds closed with sutures or staples. Dressings will be used to maintain blinding outcome assessors. The primary outcome measure will be a composite all-cause wound complication outcome measure composed of: infection, wound drainage, wound necrosis, blistering, dehiscence, suture abscess and material sensitivity reaction. An independent review board blinded to treatment assignment will adjudicate suspected complications based on clinical data. All deceased patients will also be reviewed. An interim analysis of complications will take place after half of the patients have been recruited. All data will be analyzed by a blinded statistician. Dichotomous primary and secondary outcome measures will be analyzed using the Chi-squared statistic. Continuous outcome measures will be analyzed using Student's t-test. Subgroup analysis will compare infection rates using sutures versus staples in each anatomic area (upper extremity, pelvis/acetabulum, hip/femur, knee, ankle). A further subgroup analysis will be conducted comparing trauma patients to elective surgery patients. Non-infected revision surgery will also be compared to primary surgery.

**Discussion:**

Wound closure material is an afterthought for many orthopaedic surgeons. The combined results of several comparative trials suggests that the choice of wound closure materials may have an impact on the rate of surgical site infections. However, the strength of the evidence is poor given the heterogeneity of the methods employed in previous studies. The following study protocol aims to guide surgeons in their choice of wound closure material by determining if there is a difference in complication rates in sutured and stapled wounds.

**Trial Registration:**

This trial was registered at ClinicalTrials.gov under the identifier NCT01146236 (registered June 14, 2010)

## Background

### Surgical site infections

The Centers for Disease Control (CDC) defines surgical site infections (SSIs) as superficial incisional, deep incisional and organ/space infections based on clinical and laboratory confirmation
[1]. Two-hundred and ninety-thousand SSIs occur in the United States annually following elective orthopaedic surgery resulting in $1 billion to $10 billion in additional healthcare costs according to CDC estimates from 2001. Many of these infections require long-term intravenous antibiotic treatment or further surgical interventions. It has been estimated that SSIs lead to a $4,500 per case (in 1990 dollars) increase in health care costs in the United States
[2]. Some estimates have found that surgical site infections in hip and knee replacement can incur an additional cost in excess of $28,000
[3].

### Skin closure efficacy

Animal studies have shown the mechanical equivalence of stapled and sutured wounds
[4]. Clinical studies in several specialties have not shown superiority of the cosmetic appearance of stapled or sutured wounds
[5,6]. These authors also found that patient satisfaction with the two methods of wound closure was not significantly different. In practice, it is uncommon for a patient to receive the choice of closure method pre-operatively and it is also rare to find patients with absolute preferences to one closure material over another.

### Skin closure cost-effectiveness

Several studies have mentioned the time saved in inserting and removing staples when compared with sutures
[5,7]. These studies rely on the calculation of the time saved by employing metallic staples compared to the cost of the staple insertion device. Singh et al. (2006) have previously published that staples are more than eight times more costly to insert and remove than are sutures
[8]. No study has factored the cost of complications into a cost analysis comparing sutures and metallic staples.

No comparative trial exists that has the statistical power to determine if the rate of infection in wounds closed with staples is different from that in wounds closed with sutures in orthopaedic procedures. A study in cardiac procedures suggested that subcuticular suturing in sternal wounds led to a lower overall rate of complications than stapling
[9]. Although the results of a recent meta-analysis
[10] suggest that the use of staples in hip and knee surgery should be questioned, the included studies
[7,8,11-14] did not uniformly employ experimental designs that limit bias. There is also a paucity of data to guide surgeons working in various anatomic locations on the type of wound closure material that confers the lowest risk of infection. A large, randomized and blinded prospective trial is needed to provide an answer to the question of what material is best for the closure of clean surgical wounds.

### Research question

In adult patients undergoing orthopaedic procedures does the wound closure material (sutures versus metallic staples) influence the occurrence of post-operative wound complications within the first year?

### Objectives

• To determine the best surgical skin wound closure material for use in various orthopaedic surgical procedures from a patient safety perspective.

• To identify procedures in which staple or suture closure results in an increased risk of wound complications.

• To determine if surgical wounds in trauma patients require different closure material than elective surgical wounds at distinct anatomic sites.

### Hypotheses

It is hypothesized that wounds closed with sutures and staples will have similar all-cause complication rates. The alternative hypothesis is that these wound closure methods result in different rates of complications indicating that one method is superior to the other and should be utilized for the tested procedures.

## Methods

### Study approval

This protocol was approved by the local institutional review board in May 2010. Participation is purely voluntary and withdrawal from the study after randomization will be allowed. The study was also registered at clinicaltrials.gov after institutional review board approval. Registration identification *NCT01146236* (*registered June 14, 2010)*

### Study sample

The study will be executed in five medical centers affiliated with two accredited universities. Patients will be drawn from a catchment of 2.7 million inhabitants. The study population will be a mix of rural and urban patients from diverse ethnic backgrounds. A variety of procedures will be included in the study encompassing both urgent and elective operations.

### Trial design

#### Parallel Group Randomized Controlled Trial with Economic Analysis

Recruitment of patients under the care of subspecialists in Orthopaedic Trauma, Spine, Adult Reconstruction and Upper Extremity Reconstruction will take place concurrently with the same trial infrastructure. Patients will be recruited by the office assistant, research assistant or delegate of the treating surgeon administering the surgical consent form. Verbal consent will be obtained for trauma patients unable to sign a consent form. Written consent will be obtained within 24 hours of treatment allocation. Patients eligible but not enrolled will be documented. Participant flow through the study can be seen visually in Figure 
1.

**Figure 1 F1:**
[figure not shown]
Participant flow diagram representing the planned design of the study.

### Inclusion criteria

• Adult patients (> 18 years old)

• All open orthopaedic procedures

• Any wound > 2 cm in length

### Exclusion criteria

• Open fracture

• Known nickel allergy

• Active infection (any site)

• Foot surgery (any site)

• Hand surgery (including carpal surgery)

• Arthroscopic procedures

### Interventions

• Skin closure with metallic staples

• Skin closure with suture material – type of suture (non-absorbable or absorbable) and technique (simple, horizontal mattress, vertical mattress, subcuticular) at the discretion of the surgeon.

### Method of allocation to groups

Randomization will be concealed and will be allocated at the time of skin closure. Randomization will be completed using an online randomization program. Block randomization with randomly sized blocks between eight and 12 participants will be employed to ensure an equal number of participants in each group for each subspecialty. Group assignments will be revealed by the online randomization program and the time of the randomization will be recorded electronically. Times of randomization will be compared with operative notes retrospectively to ensure concealment is being maintained.

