### Anticipated recruitment rate

In a pilot site it was found that 60% of patients approached consented to participate. A recruitment model was created taking into account expected site fatigue and differences in consenting efficiency between the United States and Canada. Based on the combined clinical volume at the five sites it is expected that the study will be completed with enrolment after 24 months of recruitment. Additional international sites are currently being developed to ensure that this target is met and to improve the generalizability of the results.

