### Clinical relevance

The inclusion of both community and tertiary centers will help to make the results of this trial immediately applicable for surgeons in diverse areas of practice. Given the inclusion of both trauma and elective patients and as a result of the powering of the study for each anatomic location, the results will also inform practitioners if there is a difference in the rate of complications as a result of wound closure material at those individual sites. The results will reflect the realities of practice in both a teaching and community environment.

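### Centre is used neither in the blocking nor in the stated primary test, so a small gain in precision is forgone; there is no bias and planned power is not reduced

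*Protocol article*

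**What the plan says.** The Method of allocation to groups section describes "Block randomization with randomly sized blocks between eight and 12 participants" and gives their purpose: they "will be employed to ensure an equal number of participants in each group for each subspecialty". The Trial design section lists four subspecialties: trauma, spine, adult reconstruction and upper extremity reconstruction. Centre is not named as a factor.

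On the setting, the Study sample section states: "The study will be executed in five medical centers affiliated with two accredited universities". The Anticipated recruitment rate section refers to both the United States and Canada and adds that "Additional international sites are currently being developed to ensure that this target is met". The Clinical relevance section says that community as well as tertiary centres take part.

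On delivery and event capture, the Interventions section leaves suture type and technique to the surgeon. The Primary outcome measure section has site coordinators find events through chart review and questionnaires. It defines infection through antibiotic use or re-operation. It also provides for uniformly trained assessors, coordinators blinded to allocation, and final determination by an independent blinded committee.

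On analysis, the Data analysis section sets Fisher's exact test for dichotomous outcomes (the Abstract says Chi-squared; both are unadjusted). It further plans stratification on potential confounders and a multivariable logistic regression, without naming the variables.

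**The concern.** Centre is a plausible predictor of the recorded outcome. Surgeons work within centres, so closure technique may cluster there. Several components of the composite depend partly on local habit, such as prescribing antibiotics or changing a dressing for drainage. Events must first be noticed by that site's coordinator.

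Where a factor predicts outcome, trials usually balance on it, adjust for it, or both. Here the stated blocking and the stated primary test do neither. Variation between centres then stays in the error of the treatment comparison, although centre is known for every patient at no cost. What is at stake is a modest amount of precision. Chance imbalance within centres is relatively largest at the half-way interim analysis and in small centres.

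**Working it through.** **No planned figure to reproduce.** The readable text gives a 25% relative risk reduction and alpha 0.05. The event rate, power and sample size are in a figure that is not available. All centre rates, centre sizes and totals below are assumptions.

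**1. How unbalanced can arms be within a centre?** Randomly permuted blocks of 8, 10 or 12 were simulated within four subspecialties, and again within each subspecialty-by-centre combination. The five centres were assumed to hold 30, 25, 20, 15 and 10% of patients, with 2,500 runs per setting. The measure is the largest value of |n1 − n0|/n over the five centres.

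| Total N | Subspecialty blocks: mean (95th percentile) | Subspecialty × centre blocks: mean (95th percentile) |
|---|---|---|
| 600 | 14% (25%) | 5% (10%) |
| 1200 | 10% (18%) | 2.4% (5%) |
| 2000 | 8% (14%) | 1.4% (3%) |

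The imbalance is real. A half-way look in a trial of 1200 would sit near the N = 600 row.

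**2. What does that imbalance cost if the analysis uses centre?** The information kept is the sum over centres of n1·n0/n, divided by N/4. Without centre blocks the simulation gives 99.3% (N = 600), 99.7% (N = 1200) and 99.8% (N = 2000). With them it is at least 99.9%. As a check, with five centres and the arms balanced overall, the expected loss is about (5 − 1)/N:
- 4/600 = 0.7%
- 4/1200 = 0.3%
- 4/2000 = 0.2%

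Blocking by centre is therefore worth under 1% once centre is in the analysis.

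**3. What does leaving centre out of the analysis cost?** At most the share of outcome variance that lies between centres: Σ w(p − p̄)² / [p̄(1 − p̄)], where w is the centre's share of patients.
- Twofold spread (13, 16, 20, 23, 26%): p̄ = 0.1795. Between-centre variance 0.00194; total 0.1795 × 0.8205 = 0.1473. Share **1.3%**.
- Fourfold spread (8, 15, 20, 28, 34%): p̄ = 0.1775. Between-centre variance 0.00736; total 0.1775 × 0.8225 = 0.1460. Share **5.0%**.
- Sensitivity, equal-sized centres: rates of 10, 15, 20, 25 and 30% give 0.0050/0.16 = 3.1%. Rates of 5, 12.5, 20, 27.5 and 35%, a sevenfold spread, give 0.01125/0.16 = 7.0%.

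**4. Translate to power.** At 80% power and two-sided alpha 0.05 the standardised effect is 1.96 + 0.84 = 2.80. Removing a share s of the variance multiplies it by 1/√(1 − s).
- s = 1.3%: 2.80 becomes 2.82; 2.82 − 1.96 = 0.86; power about 80.5%.
- s = 5.0%: 2.80 becomes 2.87; 2.87 − 1.96 = 0.91; power about 82%.
- s = 7.0%, the sevenfold case: power about 83%.

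These gains require an analysis that uses centre. An unadjusted test after centre blocking would not credit the reduced variance.

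**The case against.** The strongest reply is that nothing here is wrong. Balancing by subspecialty is a valid choice and matches the four recruitment streams. No part of the article says that closure practice or event capture differs by centre: suture choice is left to the surgeon, and the remark about "differences in consenting efficiency between the United States and Canada" belongs to a recruitment model. Uniform training and one blinded committee reduce differences in classification. The Data analysis section already plans stratification and logistic regression, and a covariate list is commonly left to an analysis plan that is not shown. The full protocol may also say more about the randomisation strata.

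Most of this stands. Differences between centres are an inference, and the safeguards are real. They are not complete, however. Training standardises definitions rather than local antibiotic or dressing practice. The committee reviews suspected complications and only a sample of patients without infection, so events that a site never flags are only partly checked. The planned regression is described as a check on confounding, while the test named for the primary outcome is unadjusted. The point therefore rests on what the article states.

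A reader might infer more: that the result could be biased by imbalance within centres, that the trial will fall short of its planned power, or that the randomisation scheme itself causes a material loss. The article supports none of these. The imbalance is random and the unadjusted test stays valid. A sample size based on overall pilot rates already includes between-centre variance. The 1% to 5% is the value of adjusting for centre; blocking alone accounts for less than 1%.

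**Conclusion.** The point holds as a small, optional improvement. As the article states the design, centre is used neither to allocate nor to compare. If event rates differ two- to fourfold across centres, a gain of about 1% to 5% of outcome variance is forgone, or roughly 0.5 to 2 percentage points of power from a base of 80%. If rates are equal across centres, there is nothing to gain. The figures depend on assumed centre sizes, an overall rate near 18% and five centres. They do not depend on the unseen sample size, except for the cost of omitting centre blocks, which is 0.7% or less from 600 patients upwards. Validity is not affected.

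**What to change.** Make the primary comparison centre-stratified and include the randomisation factor, subspecialty. Two suitable forms are a Mantel-Haenszel analysis over strata, or a logistic regression with centre and subspecialty. Lay down before unblinding how very small or late-opening centres are pooled, since further international sites are foreseen. The cost is a sentence or two in the analysis section and no new data.

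Blocking by centre as well is optional. Four subspecialties by five centres gives 20 strata, which an online program can handle, but it brings two drawbacks. More blocks stay incomplete: a 40-patient centre has about 40/4 = 10 patients per stratum, and an unfinished block of 12 can leave a difference of up to 6. Allocation also becomes somewhat more predictable within a site, where surgeons know the closures already used.

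Whichever strata are used, state that block sizes are even (8, 10 or 12). The stated range also admits 9 and 11, which cannot give equal arms.

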### Methods of blinding

Blinding of patients and providers was attempted in a pilot study. It was found that it was not feasible to blind these groups to the treatment allocation after post-operative dressings were changed, generally at postoperative day two. Additionally, post-operative radiographs revealed stapled patients in the pilot, further unblinding both providers and participants.

Outcome assessors will be blinded to the closure method through the use of long sleeved shirts, pants or a sleeve provided for the patient to wear. Blinding will be maintained by trained clinic staff aware of the purpose and methods of blinding. Participants will be asked not to reveal randomization when they become aware of treatment allocation during the course of the follow-up.

The outcomes adjudication committee will be blinded to treatment group during the determination of complications of individual patients. The data analysis team will also be blinded to the treatment groups during the synthesis of the results which will be presented as Group A and Group B in the draft manuscript.

### Primary outcome measure

The primary outcome measure will be a composite outcome encompassing all causes of wound complication. The clinical relevance of the primary outcome measure stems from the fact that the components of the composite outcome all represent occurrences that are patient important. The components consist of the following events:

1. Surgical site infection as defined by:

• Use of intravenous antibiotics

• Use of oral antibiotics

• Re-operation at same site

2. Wound drainage occurring after post-operative day two requiring a dressing change.

3. Wound Necrosis defined as blackening of the skin edges at the incision site or skin slough observed by providers or the participant.

4. Suture Abscess defined as the expulsion of deep suture material and purulent material without surrounding erythema.

5. Peri-incision Blistering defined as blistering at the edge of the incision along the entire length. Blistering at dressing tape site will be excluded from this definition, however, blistering due to wound tape application which is contiguous with the wound edge will be considered an event.

6. Wound Dehiscence as defined by the loss of apposition of the skin edges visible to the eye along the length of the incision.

7. Material Sensitivity as defined by a local reaction to metal or suture material resulting in skin changes along the entire incision length.

The primary outcome measure will be assessed during admission by review of the patient chart by site coordinators who will be blinded to the treatment allocation. Outcome assessors will be uniformly trained in the definitions of the components of the composite outcome score. Outpatient complications will be recorded through self-report questionnaires administered by site coordinators. All deceased patients will also be reviewed for occurrence wound complications. Final determination of events will be made by an independent outcomes adjudication committee based on blinded clinical data identified by the committee as necessary for the determination of complications. A sample of non-infected participants will also be reviewed by the committee as a negative control.

### Secondary outcome measures

#### Treatment preference reported by the participant

Additional unscheduled episodes of care as defined by: 

• Dressing changes by homecare/patient at home or self-reported visits to other healthcare professionals.

• Length-of-stay – Based on admission and discharge dates

• Visual analogue pain score for suture/staple removal

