### Data analysis

All anatomic sites will be analyzed together and separately using Stata (College Station, TX). Dichotomous primary and secondary outcome measures will be analyzed using Fisher’s exact test. Stratification based on potential confounding variables will be performed. A multivariable analysis employing logistic regression will be performed to assess the possible impact of empirical confounding by putative risk factors of the binary outcomes. Length of stay, visual analogue scale pain measurements and patient satisfaction data will be compared using a two-way ANOVA. Linear regression will be performed on continuous variables to assess the possible impact of empirical confounding by putative risk factors. A 4.7% level of significance will be considered significant based on the adjustment of significance level for the interim analysis.

Subgroup analyses will be performed comparing the use of sutures and staples in trauma versus elective procedures and primary versus revision procedures as appropriate.

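### Length of stay is counted from admission although patients are randomised at skin closure, so it includes pre-operative days that closure material cannot affect and will usually lose some precision

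*Protocol article*

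**What the plan says.** In the protocol article, the Secondary outcome measures section lists length of stay, defined as "Based on admission and discharge dates". The stated clock therefore starts at admission.

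The section on the method of allocation places randomisation at the end of the operation: "Randomization will be concealed and will be allocated at the time of skin closure". It adds that "the time of the randomization will be recorded electronically".

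The Study sample section describes the case mix as "encompassing both urgent and elective operations". The Trial design section recruits from orthopaedic trauma as well as from mainly reconstructive services, and provides for trauma patients who cannot sign: "Verbal consent will be obtained for trauma patients unable to sign a consent form".

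The Data analysis section states: "Length of stay, visual analogue scale pain measurements and patient satisfaction data will be compared using a two-way ANOVA". It does not name the second factor. It adds linear regression for continuous variables on risk factors that it does not list. Nothing in the article restricts the stay to post-operative days or names the pre-operative wait as a covariate.

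**The concern.** An outcome meant to show an effect of treatment should start when treatments can begin to differ. Here that moment is skin closure. Every day between admission and the operation is fixed before allocation and cannot depend on sutures or staples, yet it is added to the outcome compared between arms.

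Elective patients may be admitted on the day of surgery, while trauma patients may wait in hospital, so the added component can vary between patients. It carries no treatment signal, so it leaves the expected difference between arms unchanged and usually adds variance. What is at stake is the precision of one secondary comparison.

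**Working it through.** **Is there a figure to reproduce?** No. The article gives no mean, SD, detectable difference or power for length of stay. Its sample size rests on wound complications only. The numbers below are illustrations.

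**Structure.** Write total stay = pre + post. The pre-operative part precedes allocation, so the expected difference between arms is the same for total stay and for post-operative stay. The variance is

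Var(total) = Var(post) + Var(pre) + 2·Cov(pre, post).

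With r = SD(pre)/SD(post) and ρ the correlation between the two parts, the variance inflation is V = 1 + r² + 2ρr.

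**Independent wait (ρ = 0), assumed post-operative SD of 4 days.** V = (16 + s²)/16, where s is the SD of the wait over the whole sample. The equivalent fraction of the sample is 1/V.

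| s (days) | r | V | Rise in variance | 1/V |
|---|---|---|---|---|
| 0 | 0 | 16/16 = 1.00 | 0% | 1.00 |
| 1 | 0.25 | 17/16 = 1.06 | 6% | 0.94 |
| 2 | 0.50 | 20/16 = 1.25 | 25% | 0.80 |
| 3 | 0.75 | 25/16 = 1.56 | 56% | 0.64 |

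**In terms of power.** Assume a true effect of 0.2 post-operative SDs, 1:1 allocation and the article's 4.7% level taken as two-sided. Counting from surgery then needs 400 per arm for 80% power. With 400 per arm and the clock started at admission, power is 77.6%, 70.7% and 60.9% at r = 0.25, 0.50 and 0.75. Restoring 80% would take 425, 500 and 625 per arm.

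**Correlation.** V falls to 1 or below when ρ ≤ −r/2.

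| r | V at ρ = −0.3 | V at ρ = +0.3 |
|---|---|---|
| 0.25 | 0.91 | 1.21 |
| 0.50 | 0.95 | 1.55 |
| 0.75 | 1.11 | 2.01 |

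So the loss can vanish or reverse, or be larger than in the independent case.

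**Assumed case mix.** Let a share t of patients be trauma patients with a wait of mean m and SD s, and let elective patients wait 0 days. Then Var(pre) = t·s² + t(1 − t)·m². The first term is variation within trauma, the second variation between trauma and elective.

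- Mild case: t = 0.25, m = s = 1, post-operative SD 5. Var(pre) = 0.25 + 0.1875 = 0.4375, so V = 1 + 0.4375/25 = 1.02 and power is 79%.
- Severe case: t = 0.5, m = s = 3, post-operative SD 3. Var(pre) = 4.5 + 2.25 = 6.75, so V = 1 + 6.75/9 = 1.75 and power is 56%.

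Adjusting for urgency removes only the second term. In the severe case this leaves 1 + 4.5/9 = 1.50, and in the mild case 1 + 0.25/25 = 1.01, with the post-operative SD read as a within-group SD.

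**The case against.** Four points deserve weight.

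**Meaning of the item.** In the article's layout, length of stay sits under a lead-in about additional unscheduled care. Read literally, it could mean the stay at a readmission, which follows randomisation and would escape this criticism. The pain score at suture or staple removal sits in the same list, so the layout is probably faulty. The index admission is the likelier reading, but the ambiguity is real and the wording should settle it.

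**Existing design features.** Blocking is meant to equalise arm sizes within each subspecialty, so differences in waiting between trauma and elective services are largely balanced. The two-way ANOVA or the regression may also absorb them. This stands in part. Blocking leaves the variation in waits among trauma patients untouched. The analysis recovers the between-group part only if subspecialty or urgency is in the model, which the article does not say.

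**Bias.** A reader might infer that a chance imbalance in waiting time would pass for a treatment effect, or that the comparison is invalid. The documents do not support this. Allocation is random and concealed, the imbalance is zero in expectation, and the standard error already includes its variability. The estimate stays unbiased and type I error is not inflated.

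**Convention and importance.** Admission to discharge is what length of stay ordinarily means, and total stay may serve the economic analysis. No power is claimed for this outcome, and no stopping rule or primary conclusion depends on it. All of this stands. It makes the definition suboptimal rather than erroneous, and total stay can still be reported.

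The article is also condensed, and a fuller document might derive post-operative stay. The start point that it does state, however, is admission.

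**Conclusion.** The point holds as a minor matter of precision. The outcome as defined includes pre-randomisation days that cannot respond to closure material, and with urgent and elective patients combined this will usually weaken the comparison.

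The size cannot be derived from the documents. Under an assumed post-operative SD of 4 days and an independent wait of SD 0 to 3 days, the rise in variance is 0% to 56% before any adjustment. A reader might take the upper end to mean that the trial throws away 36% of its patients for this outcome. That would be wrong: the figure depends wholly on assumed SDs, zero correlation and an unadjusted analysis, and no loss at all is within the plausible range.

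**What to change.** Define length of stay, for the index admission, as the time from randomisation at skin closure (or from the date of surgery) to discharge. Report admission-to-surgery time as a baseline descriptor, and total stay descriptively for comparison with other studies and for the economic analysis. Set the item apart from the list of unscheduled care so that it cannot be read as readmission stay.

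The cost is a line or two of wording. The randomisation time is already recorded, and the admission and discharge dates are already collected.

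If admission to discharge must remain the analysed outcome, naming the pre-operative wait as a covariate in the linear regression would have much the same effect: with the wait in the model, the treatment coefficient for total stay equals that for post-operative stay.
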